### The type and duration of the follow-up of participants after adverse reactions

Each IM injection site will be monitored as detailed in section “Follow up assessments”. Adverse events in the participant and her baby (ies) will be monitored up to day 7 or until death or discharge whichever is earlier. Any suspected unexpected serious adverse reaction (SUSAR) will need to be reported to the Sponsor irrespective of how long after IMP administration the reaction has occurred. All adverse events will need to be followed up until it has resolved or has reached a stable state.

## Statistics and data analysis

### Sample size calculation

Using PFIM 3.2.1 software
^
51
^ and based on the population pharmacokinetic parameters determined in a meta-analysis of the different pharmacokinetic studies published in healthy volunteers and data through the IV route in trauma patients
^
13,
52
^, a sample size of 120 participants will allow estimates (relative standard errors < 30%) of the pharmacokinetic parameters of the intravenous, intramuscular and oral administration of TXA. Optimal maternal blood sampling times were evaluated and are as follows: immediately before TXA administration, and 15, 30 minutes, 1h, 2h, 4h, 8h, 12h and 24h after TXA administration. However, if in exceptional circumstances a sample cannot be taken at the optimal stated time, flexibility in blood sampling is allowed as detailed in the section “TXA administration and timing of biological samples”. The actual sampling time must be recorded.

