### Description of investigational product and justification of the dosage, route of administration, administration schedule and treatment duration

In this study, women will be randomised to four groups:

1.
**IV TXA GROUP:** 30 women will receive 1 g of TXA by IV route. IV TXA treatment rapidly achieves the plasma levels of TXA needed to inhibit fibrinolysis and prevent excessive bleeding. Pharmacological research has shown that an IV dose of 1 g TXA maintains therapeutic plasma levels for around 3 hours, the period when the risk of bleeding is greatest
^
12,
19
^. However, the TXA PK and PD in pregnant women has not been described so far.2.
**IM TXA GROUP:** 30 women will receive 1 g of TXA by IM route. Studies of IM TXA in healthy volunteers report good absorption and no adverse effects
^
11,
12
^. The dose will be given as two 5 mL (0.5 g each) injections into the thigh (rectus femoris or vastus lateralis) or buttocks (gluteal muscles) muscles, depending on a clinical assessment of muscle mass
^
12
^. The 1 g dose (10 mL) is divided to reduce the volume injected (5 mL is considered the upper limit)
^
20
^. The injections will be given using the most appropriate needle size for IM administration from the sites stock (1" between 19 - 25 gauge and from 1 ½ inches up to 3" for large adults) using the Z-track method to seal the medication in the muscle
^
20
^.3.
**TXA SOLUTION ORALLY:** 30 women will receive 4 g of TXA oral solution. The dose was selected because of the 50% oral bioavailability and because previous and preliminary PK data show that the absorption through the oral route is much slower than through the IV or IM routes, with much lower maximal concentration (Cmax)
^
12,
13,
19,
21
^. Therefore, higher doses are needed to reach therapeutic levels, according to simulations. The oral route (tablets or solutions) is well characterised
^
22–
24
^, but oral TXA PK and PD in pregnant women have not been described so far.4.
**NO TXA CONTROL:** 30 women will receive no TXA and will be the control group for PD, blood loss and safety data.

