### Randomisation

After collecting baseline data, enrolled participants will be randomised into one of the four groups described in “Description of investigational product and justification of the dosage, route of administration, administration schedule and treatment duration”. The sequence for each dosing cohort will be created using computer-generated random numbers, using blocking to ensure the required balance in the allocation of participants to treatment arms. The allocation ratio will be 1:1:1:1. 

An IT coding expert supported by a statistician who are not involved in the conduct of the trial will prepare the randomisation codes. Eligibility will be confirmed and randomisation done via an online database. Once the code is generated, the trial intervention will be prepared and administered by a trained trial team member. Participants and all trial staff will be blind to treatment allocation until randomisation is completed.

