### Collection and storage of biological samples

Only one blood sample for PK analysis will be collected at baseline for women who are randomised to receiving no TXA. Samples for D-dimer, full blood count (FBC) and renal function will be collected.

Maternal blood will be taken from a cannula to avoid multiple venepuncture as follows:

Two samples of 3mL each will be taken for FBC and two samples of 3mL each for renal function. Blood samples will be collected in purple top EDTA tubes for FBC and yellow top tubes with separation gel and clot activator for renal function.

Five samples for D-dimer of 3 mL for each sample of blood to be taken in collection blue top tubes containing 3.2% sodium citrate. Blood samples for D-dimer, FBC, and renal function will be collected from the hospitals and analysed by a local central laboratory. The laboratory will be asked to store the sample used for D-dimer analysis until the end of trial to allow for repeat tests if needed. In the event of failure of any of the PK samples, this will be used as a back-up and will be destroyed at the end of the trial.

Each maternal PK sample require about 20 µL of blood taken using a Mitra
^®^ cartridge from a finger prick (2 × 10 µL samples taken on the 2 cartridges of the same device to have one primary and one confirmation sample if needed). Sites will be provided with written procedures on how to obtain the blood sample using the Mitra
^®^ cartridge. Cartridges will be labelled with the date and time the sample was taken and with the participant Study Identification number.

The total volume of blood taken (less than 35 mL) should have no clinical impact on the participant.

To obtain the umbilical PK blood sample, once the umbilical cord is clamped, it is wiped with antiseptic and a syringe and needle is inserted into the vein in the umbilical cord to withdraw a small amount of blood. PK samples from the umbilical cord and neonates will also be taken using the Mitra
^®^ cartridge system as described above.

A blood sample from the neonate (2×10 µL) will be taken using the Mitra
^®^ cartridge at the time of the routine clinical heel prick test to avoid additional heel pricks.

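### The precision claim (relative standard errors below 30%) is attached to 120 participants, but the four-arm plan yields 90 women who can inform the PK parameters; a missed target is not shown

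*Protocol article*

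**What the plan says.** The Sample size calculation section of the protocol article states that "a sample size of 120 participants will allow estimates (relative standard errors < 30%) of the pharmacokinetic parameters" and continues "of the intravenous, intramuscular and oral administration of TXA". The calculation was made "Using PFIM 3.2.1 software" and was "based on the population pharmacokinetic parameters determined in a meta-analysis of the different pharmacokinetic studies published in healthy volunteers", together with IV data from trauma patients. The maternal sampling times are "immediately before TXA administration, and 15, 30 minutes, 1h, 2h, 4h, 8h, 12h and 24h after TXA administration", which is one pre-dose and eight post-dose samples.

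The 120 are spread over four arms. Under Randomisation, "The allocation ratio will be 1:1:1:1". The Description of trial population gives 30 women to each of IV, IM, oral and no TXA. The section on the investigational product defines the fourth group: "30 women will receive no TXA and will be the control group for PD, blood loss and safety data". PK is not among its purposes. Collection and storage of biological samples adds: "Only one blood sample for PK analysis will be collected at baseline for women who are randomised to receiving no TXA".

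The Pharmacokinetic analysis section admits only women who took the full TXA dose, did not vomit an oral dose in the first hour, and have six or more PK samples after TXA. The Planned recruitment rate section sets the target at 120 evaluable women and defines evaluable by the full dose and six or more PK samples after randomisation. The Abstract also sets 120 women with six or more PK samples as the point at which randomisation ends.

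**The concern.** Population PK is the primary objective, and this sentence is the article's only justification of the trial's size. It credits the precision of three routes' parameters to 120 women, although a quarter of them receive no drug and are not sampled after baseline. Such women carry no information on clearance, volume, absorption or bioavailability.

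Anyone who later judges whether the trial was large enough, or plans another from it, would start from the wrong number. The same miscount reaches the recruitment rule, where it affects when enrolment can be declared complete.

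**Working it through.** **Inputs from the article.** Total 120; four arms at 1:1:1:1, 30 each; one arm untreated, with one baseline PK sample; PK set limited to dosed women with at least six post-dose samples; precision bound of 30%.

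**Can the stated figure be reproduced?** No. A bound on relative standard error (RSE) from an optimal-design program depends on the structural model, fixed effects, between-subject variances, residual error and number of women per design group. The article gives none of these. What can be checked is the headcount.

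**Headcount.**
- Randomised: 4 x 30 = 120, which matches the stated total.
- Dosed, and so able to enter the PK set: 3 x 30 = 90, which does not match 120.
- Share that can inform PK: 90/120 = 75%.
- Route-specific absorption parameters rest on 30 women per route.

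**Recruitment rule taken literally.** If 120 women must each have at least six PK samples, and only three arms in four can supply them, the number randomised is 120/0.75 = 160, or 40 per arm. That contradicts 30 per arm.

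**Effect on precision.** For a fixed sampling schedule per woman and fixed arm proportions, Fisher information is proportional to the number of women, so RSE is proportional to 1/sqrt(N). Moving from 120 dosed women (40 per route) to 90 (30 per route) multiplies every RSE by

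sqrt(120/90) = 1.155.

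The factor is the same for shared and route-specific parameters, since 120/90 = 40/30.

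| RSE if 120 women were dosed | RSE with 90 dosed |
|---|---|
| 20% | 23.1% |
| 25% | 28.9% |
| 26.0% | 30.0% |
| 28% | 32.3% |
| 30% | 34.6% |

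The break-even is 30%/1.155 = 26.0%: a parameter below this at 120 stays under 30% at 90.

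**Possible cases.**
1. The program was run on 3 x 30 dosed women: RSEs do not change, and only the stated number is wrong.
2. It was run on 120 dosed women and the largest RSE was below 26.0%: RSEs rise, but the 30% bound still holds.
3. It was run on 120 dosed women and some parameter exceeded 26.0%: that parameter passes 30%, reaching at most 34.6%.

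The article does not say which case applies.

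**The case against.** The strongest reply is that 120 is simply the trial total: randomising 120 women equally gives 30 per route, and that design gives RSEs under 30%. The sentence does not say that 120 women are dosed, and other sections state openly who is dosed, sampled and analysed. Taken alone, the sentence allows this reading. It is undercut by the Abstract and the Planned recruitment rate section, which require PK samples from all 120; the latter also requires the full dose. There the controls really are counted as PK-evaluable. This does not show what number was entered in the software, so case 1 remains possible.

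A second reply is that the software inputs and the RSE for each parameter belong in the full protocol, an additional file not shown here. That is right, and their absence is no part of this point. The conflict is between numbers that the article itself prints.

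Two stronger readings are tempting and should not be drawn. A reader might infer that the trial misses its 30% target, or that its true RSE is 34.6%. That needs both a run on 120 dosed women and a parameter at the bound; the article supports neither, and gives only an upper limit. A reader might also take 90 as a strict ceiling. The rules on replacing participants keep the data of replaced women, and one replaced only because her caesarean section was delayed could still meet the PK criteria. The realised PK set could slightly exceed 90; the planned number does not change.

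**Conclusion.** The point holds as a headcount contradiction, with high confidence. The plan attaches its PK precision to 120 women, while its own arm sizes, control sampling and PK analysis set give a planned 90, with 30 per route. The recruitment target repeats the miscount.

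The consequence for precision is not established. It ranges from none (cases 1 and 2 both keep the 30% bound) to a 15.5% relative rise in every RSE, with 34.6% as the upper limit. That range rests on the usual scaling of information with the number of women and on an unchanged schedule and equal split across routes. The wording needs correcting in every case, because it supports the primary objective.

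**What to change.** 1. Confirm which number of dosed women was used in the design evaluation. If it was not 30 IV + 30 IM + 30 oral, re-run it at those numbers with the eight post-dose times.
2. Restate the claim for 90 TXA-treated women, 30 per route, with the RSE bound that holds at that number.
3. Say that the 30 controls are there for D-dimer, blood loss and safety and carry no PK precision claim.
4. In the Abstract and the Planned recruitment rate section, apply the six-sample rule to the three TXA arms only, and give controls their own completion rule.

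The cost is at most one software run and a few reworded sentences. No extra patients are needed, and allocation, sampling and the PK analysis stay as they are. The one downside is that the stated precision may become slightly less favourable.

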### Planned recruitment rate

Pregnant women will be enrolled until 120 participants with fully evaluable data are included. Evaluable participants must receive the full dose, not vomit the oral dose within 1 hour of administration, and have at least six post randomisation PK blood samples.

### Statistical analysis plan

All statistical calculations will be performed using STATA, unless otherwise specified. All data will be presented in the form of summaries sorted by treatment group (cohort) and participant ID. Tabular summaries will be presented based on the following grouping: IM, IV, Oral solution and No TXA.

For continuous variables, summary statistics will include sample size, mean, standard deviation, median, minimum, and maximum values. Frequencies and percentages will be calculated for categorical variables.

### Pharmacokinetic analysis

All participants who receive the full dose of TXA and did not vomit the oral dose within the first hour and have at least six PK samples obtained after TXA administration to determine maternal plasma concentrations of TXA will be included in the PK data analysis. The actual blood sampling times will be recorded and used in calculations for PK parameter estimation. 

TXA time-courses will be analysed using the nonlinear mixed effect modelling software program
Monolix 2020R1 version
^
53
^, as previously described
^
52,
54–
56
^. Briefly, parameters will be estimated by computing the maximum likelihood estimator of the parameters without any approximation of the model (no linearization) using the stochastic approximation expectation maximization (SAEM) algorithm combined to a Markov chain Monte Carlo (MCMC) procedure (to ensure full convergence, the MCMC will be fixed to 20 and the iteration number to 1000). Different error models will be investigated (i.e. multiplicative, proportional and/or additive error models) to describe residual variabilities (expressed as σ, square root of σ
^2^), and the between-subject variabilities (expressed as ω, square root of the variance ω
^2^) will be ascribed to an exponential model. The Bayesian information criterion (BIC) will be used to test different hypotheses regarding the model, i.e.:

i.covariate effect(s) on pharmacokinetic parameter(s)ii.residual variability model (proportional versus proportional plus additive model)iii.structure of the variance-covariance matrix for the ω parameters.

Main covariates of interest in the population will be age, bodyweight (BW) and renal function, IV fluid and blood transfusion volume. Parameter estimates will be standardised for a mean standard covariate using an allometric model: P
_i_ = P
_STD_ x (COV
_i_/COV
_STD_)
^PWR^ where P
_STD_ is the standard value of parameter and P
_i_ and COV
_i_ are the parameter and covariate values of the i
^th^ individual. The PWR exponents may be estimated from the data. However, for bodyweight, allometric scaling theory dictates that these are typically 0.75 and 1 for clearance and volumes terms, respectively
^
46
^. The goodness-of-fit of each model will be evaluated by visual inspection of the individual concentration-time courses, the observed-predicted (population and individual) concentration scatter plots and the prediction-corrected visual predictive checks.

**Placenta transfer and neonate heel prick PK levels:** Concentrations will be presented in tabular form with mean, median, standard deviation and range as appropriate. For each time point, comparisons across groups will be done using the analysis of variance. We will adjust for time between drug administration and sampling. Where both an umbilical cord and neonate heel prick sample is available, these will be used to build a PK model with gestational age and birth weight as the main covariates.

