### TXA administration and timing of biological samples

The time of the TXA administration is T
_0_. One blood sample will be taken for PK prior to drug administration.

Post TXA administration blood samples will be taken at different time points during 24 h as per the schedules in
Figure 3. We understand that the care of the participant takes priority over the sampling schema and that sample times will inevitably differ from those indicated. If it is not possible to obtain a sample at the scheduled time, the sample should be collected as soon as feasible with the exact time of collection recorded. Reasons for any delay will be recorded. Where there are less than six evaluable PK samples obtained after TXA administration from a participant, this participant will be replaced in the study.

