### Premature exit of trial participant

Participants may exit the study at any time and for any reason. A previously given consent can be withdrawn. The investigator can withdraw a participant from the trial for any safety reason or if it is in the participant's best interest.

If a participant exits the trial prematurely or withdraws consent or refuses consent for continuation, data collected up to time of premature exit will be used. Participants who withdraw from the trial with less than six post treatment PK samples will be replaced to ensure the four intervention groups remain balanced.

**
*Monitoring participants after the premature termination of treatment.*
** In case of an adverse event to the participant or her baby, the investigator will complete an adverse event report and monitor the event until the end of her participation in the research or until it has resolved or reached a stable state.

**
*Procedure for replacing participants.*
** If consent procedures are complete but the TXA dose is not given in full, the participant will be replaced.

When oral TXA is given and the participant vomits within the first hour of receiving the intervention, this participant will be replaced in the study. However, data collection for the participant will continue to the trial end.

Where the CS is delayed and takes place more than 2 hours after the administration of the intervention, the participant will be replaced in the study. However, data collection for the participant will continue to the trial end.

If a participant receives the TXA dose but there are less than six post treatment evaluable PK samples obtained after TXA administration, this participant will be replaced in the study. However, data collection for the participant will continue to the trial end.

Data collected from the replaced participants will be used.

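### The primary PK set drops early vomiters and women with fewer than six samples, while the replacement rules say replaced women's data will be used without naming the analysis; usable data are lost and oral exposure may look too high

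*Protocol article*

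**What the plan says.** The primary endpoint is maternal blood TXA concentration over time, and the Pharmacokinetic analysis section fixes who enters that analysis. It takes "All participants who receive the full dose of TXA and did not vomit the oral dose within the first hour" who also "have at least six PK samples obtained after TXA administration to determine maternal plasma concentrations of TXA will be included in the PK data analysis". Planned recruitment rate uses the same three conditions to define an evaluable woman.

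Premature exit of trial participant, with its part on replacing participants, lists four grounds for replacement:

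- Incomplete dose: "If consent procedures are complete but the TXA dose is not given in full, the participant will be replaced".
- Early vomiting: "When oral TXA is given and the participant vomits within the first hour of receiving the intervention, this participant will be replaced in the study".
- A caesarean section more than 2 hours after the intervention.
- Fewer than six evaluable post-dose samples.

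For the last three, data collection continues to the end of the trial. The list closes with "Data collected from the replaced participants will be used". For women who leave early, the same section says "data collected up to time of premature exit will be used". Neither sentence names an analysis.

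Sample size calculation schedules eight post-dose samples, from 15 minutes to 24 hours. The section on TXA administration and sample timing accepts that "the care of the participant takes priority over the sampling schema", and allows late samples with the exact time recorded. The Pharmacokinetic analysis section uses actual sampling times in a nonlinear mixed-effects model.

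**The concern.** There are three linked problems.

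First, the two sections leave the primary dataset open to two readings. One analyst could apply the three conditions literally. Another could follow the replacement rules and bring replaced women in. Women replaced for a delayed caesarean section are not excluded by the Pharmacokinetic analysis section, so one kind of replaced woman enters the PK model and the other three do not, with no reason given.

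Second, the six-sample minimum serves no estimation purpose. A mixed-effects model borrows strength across women, and a woman with three, four or five timed concentrations still informs it.

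Third, the vomiting condition can remove women from one arm only. The safety section lists vomiting among the drug's most common side effects. The article's stated aim is to learn whether the IM and oral routes are absorbed well enough to inhibit fibrinolysis, and its hypothesis is a level of at least 10 mg/L within about 30 minutes. If women who lose part of the oral dose appear in no exposure result, readers judging whether the route is usable will see it at its best.

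**Working it through.** **The plan's own figure.** Four groups of 30 give 4 × 30 = 120 women, of whom 3 × 30 = 90 receive TXA. The stated precision (relative standard errors below 30%) cannot be reproduced, because the PK parameters, variances and residual error entered into PFIM are not in the article. The point does not depend on it.

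**Replacement ground against PK set.**

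| Replaced because of | Data collection continues? | In the PK set as written? |
|---|---|---|
| Incomplete dose | Not stated | No |
| Oral dose vomited within 1 hour | Yes | No |
| Caesarean section after more than 2 hours | Yes | Yes, if the other conditions are met |
| Fewer than six evaluable samples | Yes | No |

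**What the six-sample rule discards.** Eight post-dose samples are scheduled, so a woman leaves the set when three or more are missing. She may then have up to 8 − 3 = 5 valid timed concentrations. The article gives no missing-sample rate. As an illustration, if each sample is missed independently with probability q, the excluded share is

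1 − [(1−q)^8 + 8q(1−q)^7 + 28q²(1−q)^6].

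- q = 10%: 1 − (0.4305 + 0.3826 + 0.1488) = 3.8%.
- q = 20%: 1 − (0.1678 + 0.3355 + 0.2936) = 20.3%.

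**What the vomiting rule does to oral exposure.** Set mean exposure in non-vomiters to 1. Let v be the share who vomit within 1 hour and f the fraction of normal exposure they retain. The mean in all women given the oral dose is 1 − v(1−f). The analysed set therefore exceeds it by the ratio 1 / [1 − v(1−f)]. Both v and f are assumed, since the article gives neither.

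| v | f = 0 | f = 0.5 |
|---|---|---|
| 5% | 1/0.95 = 1.05 | 1/0.975 = 1.03 |
| 10% | 1/0.90 = 1.11 | 1/0.95 = 1.05 |
| 20% | 1/0.80 = 1.25 | 1/0.90 = 1.11 |

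The range is about 3% to 25%. The IV and IM arms have no corresponding exclusion.

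**The case against.** **The sections do not collide.** A reader might infer a flat contradiction. The documents do not support that. The replacement rules name no analysis, and the D-dimer, safety, blood-loss and PPH sections set no such exclusions. Using replaced women's data there and not in the PK model would satisfy both sections. This objection stands; what remains is an ambiguity.

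**A clean PK set is legitimate.** The retained dose of an early vomiter is unknown, so leaving her out of the base parameter fit is defensible, and replacement protects the numbers: 90 evaluable TXA women still supply 90 × 6 = 540 to 90 × 8 = 720 post-dose concentrations. Stored D-dimer samples also serve as back-up if a PK sample fails. All of this stands. It does not justify dropping women with three to five good samples, nor having no exposure summary for everyone dosed.

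**Missing samples and bleeding.** A reader might infer that samples will be missed mainly in women who bleed, so that the set describes only uneventful courses. The article does not say so. It says only that care comes first and that late samples are accepted. PPH and transfusion exclude nobody, every participant has a PPH risk factor, and IV fluid and transfusion volume are planned covariates. Even if the link existed, its effect would probably be small. Suppose 10% to 20% bleed, their relative exposure is 0.70 to 0.85, and 30% to 50% of them are excluded against 5% of the others. At the upper end, the mean over all women is 0.2 × 0.70 + 0.8 = 0.94. The mean over those kept is (0.2 × 0.5 × 0.70 + 0.8 × 0.95) / (0.2 × 0.5 + 0.8 × 0.95) = 0.83/0.86 = 0.965, a ratio of 1.03. At the lower end the ratio is 1.00.

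**Incomplete dose.** This is a dosing event, not a consequence of treatment. Continued data collection is not promised for these women, and the compliance section asks for the reason but does not mention the amount given. They may have nothing to model.

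**Target attainment.** A reader might want the bias expressed as a proportion reaching 10 mg/L. The article specifies no such analysis, so no percentage of that kind can be derived from it.

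**Conclusion.** The concern holds in a limited form. The article fixes the primary PK set by conditions that a mixed-effects model does not need in full, and it leaves unclear whether the data it continues to collect from replaced women belong in that set. The six-sample rule can cost up to five valid concentrations per excluded woman; how many women this affects is unknown. The vomiting rule can only raise apparent oral exposure relative to all women given the oral dose, provided vomiting lowers exposure, which is likely but not documented here. The illustrated size, about 3% to 25% of mean exposure, rests entirely on the assumed vomiting shares and retained fractions. This is an inexpensive improvement to the analysis, not a flaw that invalidates the trial.

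**What to change.** 1. Use the full-dose, vomiting and six-sample criteria only to decide who is replaced.
2. Include in the population PK model every woman given trial TXA with at least one timed post-dose sample, including those with fewer than six. Include partly dosed women only where both the amount given and samples are recorded.
3. For women who vomit within 1 hour, either estimate a separate bioavailability effect or leave them out of the base parameter fit. In either case report their observed concentrations and an exposure summary by route for all women dosed. With recruitment to 30 evaluable women in the oral arm, 5% to 20% vomiting would mean roughly 32 to 38 women dosed (30/0.95 to 30/0.80, rounded up), so about 2 to 8 vomiters. That may be too few for a stable separate effect, which is why the second option is offered.
4. Keep the set now described in the Pharmacokinetic analysis section as a sensitivity analysis.
5. State in the replacement rules which analyses use replaced women's data, and say explicitly how women with a delayed caesarean section are handled, so that those rules, Planned recruitment rate and Pharmacokinetic analysis agree.

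The cost is revised wording, one extra model run and slightly more variable oral-arm estimates. For vomiters and short-sampled women the article already continues data collection, so no new sampling is needed.
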